#### Data analysis

The effect of CBD relative to placebo on the outcome of 12-week positive PANSS score will be analysed using mixed model repeated measures with fixed effects for treatment arm, time, study site, and treatment arm × time interaction. A random intercept will be included to account for variation in scores between participants. An unstructured variance–covariance structure will be assumed, and where there are convergence issues, a compound symmetry covariance structure will be used instead. Consistent with a treatment policy approach (ICH E9 R1), all participant data will be analysed regardless of missed assessment data, withdrawal from the treatment arm or use of rescue medication (i.e. intention to treat). Suitable contrasts will be used to evaluate the difference in mean total PANSS scores at the primary endpoint (week 12). Missing data will be imputed using multiple imputation by chained equations (MICE) under an assumption of missing at random. A sensitivity analysis will be conducted using a tipping point analysis and the delta adjustment method (e.g. MICE ± 1 PANSS positive score point increments) to evaluate the robustness of the model to the underlying assumptions of missingness. A further sensitivity analysis will be conducted using an alternative analysis of covariance model plus MICE. All other secondary and/or exploratory outcomes will be analysed using the same approach. The number needed to treat will be calculated based on the proportion of participants in each arm who achieve >20% reduction in total PANSS score. Use of co-medications, clozapine/norclozapine levels, and presence of THC and THC metabolites will be considered in the analysis.

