### Statistical analysis

#### Sample size

A power analysis was conducted based on the mean difference in positive PANSS score between treatment arms at the primary analysis endpoint (12 weeks post-baseline assessment). A mean difference in positive PANSS score of 1.30 at 8 weeks^17^ (extrapolated to a conservative difference of −1.8 at 12 weeks, assuming a logarithmic trend over a linear trend), standard deviation difference of 3.739 (Cohen's *d* effect size of 0.48), correlation between assessment timepoints of 0.6, *α* = 0.025 (one-sided), and 1 − *β* = 0.8, with repeated measures (four assessment timepoints) and analysis of variance (ANOVA) as the planned analysis with pairwise contrast, yielded a requirement of 70 participants. Allowing for 20% dropout and rounding up to the nearest multiple of treatment arms (*n* = 2) suggests that a minimum sample of 88 participants is required overall.

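### The primary model adds a random participant intercept to an unstructured covariance; one of the two is redundant, and the redundancy invites an avoidable switch to compound symmetry

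*Protocol article*

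**What the plan says.** The Data analysis section of the protocol article specifies a mixed model for repeated measures with "fixed effects for treatment arm, time, study site, and treatment arm × time interaction". It continues: "A random intercept will be included to account for variation in scores between participants. An unstructured variance–covariance structure will be assumed". The only fallback is: "where there are convergence issues, a compound symmetry covariance structure will be used instead". The section does not say which matrix is unstructured, or whether baseline is one of the modelled responses. On missing data it says: "Missing data will be imputed using multiple imputation by chained equations (MICE) under an assumption of missing at random". It applies the same approach to all other outcomes.

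Table 1 schedules PANSS at weeks 0, 4, 8 and 12. The Sample size section counts four timepoints and uses one SD (3.739) and a "correlation between assessment timepoints of 0.6". No SD or correlation is given for individual visits.

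**The concern.** An unstructured residual covariance already gives each visit its own variance and each pair of visits its own covariance. All between-participant variation is inside it, so a random intercept asks the data to split off a part that they cannot distinguish.

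The split is of no interest in itself. It matters because a singular Hessian or failed convergence is the usual symptom, and that is the event which triggers the fallback. A software message caused by the wording of the model, not by the data, could then decide the primary covariance structure. The structure it would select assumes equal variance at every visit and equal correlation at every lag. The standard error of the week-12 contrast would come from a variance pooled over visits.

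**Working it through.** **Identifiability.** Write the marginal covariance as V = σ_b²·J + R, where J is a matrix of ones, σ_b² the intercept variance and R the residual matrix.

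- *R unstructured.* For any σ_b² that leaves V − σ_b²·J positive definite, R = V − σ_b²·J gives the same V and therefore the same likelihood. With four visits R has 4·5/2 = 10 parameters, and the intercept makes 11; the rank is 10. With three responses (weeks 4, 8, 12) it is 3·4/2 + 1 = 7, rank 6. For outcomes that Table 1 schedules only at weeks 0 and 12 it is 2·3/2 + 1 = 4 for 3 quantities.
- *R compound symmetric.* V = σ_b²·J + (σ_c·J + σ_e²·I). Only σ_b² + σ_c and σ_e² can be identified: 3 parameters, rank 2. The fallback is redundant too if the intercept is kept.
- *Unstructured meaning the random-effects matrix.* One random intercept gives a 1 × 1 matrix. Unstructured and compound symmetry are then the same thing.

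Numerical check on one simulated data set of 88 participants × 4 visits: the maximised log-likelihood was −525.6016 at each intercept variance tried (0, 1, 3, 5 and about 7.5), and one Hessian eigenvalue was zero to numerical accuracy (about −1×10⁻⁶). Without the intercept the smallest eigenvalue was 4.2. The fitted marginal covariance and fixed effects are the same either way.

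**Fallback under the plan's own assumptions.** Inputs: SD 3.739, read as common to all visits; correlation 0.6; 88/2 = 44 per arm; complete data, as after imputation; site ignored. The week-12 standard error is 3.739·√(2/44) = 0.797. Compound symmetry gives the same 0.797, so the ratio is 1.00 and the one-sided error is 0.025.

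**Fallback if SDs differ by visit.** The visit patterns here are assumptions, because the documents give none. Ratio of compound-symmetry SE to true SE = √(mean of SD² over modelled visits) / SD at week 12. One-sided error = 1 − Φ(1.96 × ratio).

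| Assumed SDs | Responses | SE ratio | One-sided error |
|---|---|---|---|
| 3.0 / 3.4 / 3.6 / 3.739 | weeks 0–12 | √11.875/3.739 = 0.922 | 0.035 |
| same | weeks 4–12 | √12.833/3.739 = 0.958 | 0.030 |
| 2.8 / 3.3 / 3.74 / 4.1 | weeks 0–12 | √12.382/4.1 = 0.858 | 0.046 |
| same | weeks 4–12 | √13.896/4.1 = 0.909 | 0.037 |
| linear growth, week 12/baseline = 1.25 | weeks 0–12 | 0.900/0.996 = 0.903 | 0.038 |
| linear growth, ratio 1.5 | weeks 0–12 | 1.008/1.196 = 0.843 | 0.049 |
| linear shrinkage, ratio 0.8 | weeks 0–12 | 0.720/0.638 = 1.129 | 0.0135 |

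With exchangeable correlation 0.6, simulation (20,000 trials per scenario) gave 0.024, 0.037 and 0.047 for compound symmetry at SD ratios 1, 1.25 and 1.5. An unstructured covariance without the intercept gave 0.023 to 0.024 in all five scenarios simulated.

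**The case against.** The strongest reply is that little of consequence is broken. Only the intercept variance is unidentified. The marginal covariance and the week-12 contrast are identified, and software that sets the variance to zero returns the correct unstructured result. This stands: failure is invited, not certain. It is also fair to ask why redundancy should stop the first model and not the second. Either may be resolved by the software or neither, so the outcome depends on the package and its settings.

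Second, a reader might infer that the primary P-value will be too small. The documents do not support that. Compound symmetry matches the only covariance pattern they contain. The entry threshold of 60 in Box 1 is on total PANSS, so any narrowing of baseline positive-subscale scores is indirect and of unknown size. Nothing in the documents shows that spread widens on treatment, and if it shrinks the test is conservative.

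Third, the planned sensitivity analysis by analysis of covariance, if fitted to week-12 scores, does not pool variance over visits and would probably expose a badly wrong standard error. That is a useful partial check, but it does not repair the primary analysis.

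Fourth, degrees-of-freedom methods and a ladder of fallback structures commonly sit in the statistical analysis plan. That also stands, so the full ladder is offered below as a preference. The redundancy is different: the article states it, and it is wrong as stated.

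**Conclusion.** The primary model is mis-specified on either reading of unstructured: an unidentifiable variance on one, an empty choice of structure on the other. This is algebra and needs no assumption about the data.

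The consequence is conditional. The week-12 effect can still be estimated, but a warning that triggers the fallback is to be expected. If the analysis does move to compound symmetry, the one-sided error is 0.025 under the plan's constant SD and 0.6 correlation, about 0.030 to 0.049 under the assumed SD growth (depending on its size and on whether baseline is a response), and about 0.0135 under the assumed shrinkage. These figures rest on assumed visit SDs, 44 complete participants per arm and no site adjustment. A claim that the standard error will be wrong, or wrong in a known direction, goes further than the documents allow.

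**What to change.** Drop the random intercept, and state that the unstructured matrix is the within-participant residual covariance. The fitted marginal covariance and fixed effects do not change, so nothing is lost. Because the imputed data sets are complete, an unstructured matrix of this size should then rarely cause difficulty. Apply the same wording to the other outcomes, and say whether baseline is a modelled response.

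Preferably, also replace the direct jump to compound symmetry with a pre-specified fallback that lets variances differ by visit, for example heterogeneous Toeplitz and then heterogeneous compound symmetry. If robust standard errors accompany a structured fallback, specify a small-sample correction: uncorrected sandwich errors tend to be too small at looks such as the first, with n = 22.

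The cost is a few words in the protocol or analysis plan, best settled before the model is fitted to unblinded data. There is no effect on sample size, visits or data collection.

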**Method:**

This is a 12-week randomised, placebo-controlled, double-blind, parallel-group trial (registration number: ACTRN12622001112752). We will recruit 88 individuals with clozapine-resistant schizophrenia, randomised (1:1) to 1000 mg daily CBD versus placebo. Eligible individuals will be aged between 18 and 64 years, fulfil DSM-IV criteria for schizophrenia or schizoaffective disorder, have a total PANSS (Positive and Negative Syndrome Scale) score ≥60, have received oral clozapine for at least 18 weeks and have a clozapine level of >350 ng/mL. Interim analyses will be conducted at 25, 50 and 75% recruitment; these will also provide an opportunity to reallocate participants dependent on conditional power. The primary endpoint will be the difference in PANSS positive scores at the end of week 12. Secondary endpoints include depression, anxiety, sleep, quality of life, alcohol consumption, change in weight and metabolic syndrome components, and neurocognitive measures, as well as safety and tolerability.

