## Study objectives

The aim of this study is to examine the clinical efficacy of an add-on CBD treatment in patients with clozapine-resistant schizophrenia. The primary objective is to determine the impact of 12-week treatment with CBD, compared with placebo, on scores on the positive subscale of PANSS in patients with clozapine-resistant schizophrenia.

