## Hypothesis

We hypothesise that participants allocated to the intervention group (1000 mg daily CBD treatment) will demonstrate a reduction in PANSS positive scores at the end of week 12 compared with participants receiving placebo.

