#### Secondary

Secondary outcomes included the impact of 1000 mg daily CBD treatment over 12 weeks compared with placebo on PANSS total scores and other PANSS subscales; depression; anxiety; sleep; quality of life; alcohol consumption; changes in weight and metabolic syndrome components including waist circumference, haemoglobin A1C (HbA1c), high-density lipoprotein (HDL), low-density lipoprotein (LDL), body mass index (BMI), triglycerides, blood pressure, hip-to-waist ratio, electrolyte and liver function tests (ELFTs), non-alcoholic fatty liver disease (NAFLD) scores, fibrosis-4 scores (FIB-4), heart rate, diet and appetite, and physical activity; endpoint clozapine and norclozapine levels compared with baseline; and neurocognitive measures. Additional aims were to determine the safety and tolerability over 12 weeks of 1000 mg daily CBD in patients with clozapine-resistant schizophrenia compared with placebo as measured by the number of participants reported to have dropped out, number of adverse events reported, and scores from a structured qualitative interview with participants about their experience with the study investigational product using the Systematic Assessment for Treatment Emergent Events – Systematic Inquiry (SAFTEE-SI).^24^

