### Efficacy measures

The PANSS positive score will be the primary outcome.^26^ Secondary outcome measures will include the following:
PANSS total and other subscale scores (negative scale and general psychopathology scale);^26^Global Assessment of Function: a numeric scale from 1 to 100 used by clinicians to subjectively rate participants' social, occupational and psychological functioning;^27^Simple Physical Activity Questionnaire: a five-item instrument designed to measure physical activity and sedentary behaviour in various populations, including clinical samples with high levels of sedentary behaviour;^28^Assessment of Quality of Life 4 Dimensions: a 12-item instrument that captures four dimensions of quality of life, comprising independent living, mental health, relationships and senses;^29^Clinical Global Impression: a measure of symptom severity, treatment response and treatment efficacy in treatment studies of people with schizophrenia;^30^Test of Premorbid Functioning: a measure of pre-injury IQ and memory ability;^31^Brief Assessment of Cognition in Schizophrenia (BACS) Verbal Memory and Learning: a measure of episodic verbal learning memory;^32^BACS digit sequencing task: a measure of working memory;^32^BACS symbol coding task: a measure of non-verbal functions such as attention, flexibility, speed of processing and abstract reasoning;^32^BACS semantic and letter fluency: a verbal fluency test that measures spontaneous production of words that belong to the same category or begin with the same letter;^32^Hamilton Rating Scale for Anxiety: a measure of anxiety symptom severity;^33^Calgary Depression Scale for Schizophrenia: a nine-item measure of depression in schizophrenia, independent of psychosis symptoms;^34^Trail Making Test: a neuropsychological test of visual attention and task switching that can provide information about visual search speed, scanning and speed of processing, mental flexibility, and executive functioning;^35^Food Craving Inventory: a 28-item self-reported measure of general and specific food cravings;^36^Alcohol Use Disorders Identification Test: a ten-item screening tool to assess alcohol consumption, behaviours, and problems associated with alcohol use;^37^Pittsburgh Sleep Quality Index: a 19-item self-reported measure of overall sleep quality assessing seven domains comprising subjective sleep quality, sleep latency, sleep duration, habitual sleep efficiency, sleep disturbances, use of sleeping medication and daytime dysfunction;^38^physical health measures including, BMI, waist circumference, waist-to-hip ratio, heart rate, blood pressure, HDL, LDL, triglycerides, total cholesterol, HbA1c, ELFTs, NAFLD and FIB-4.

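### The sentence defining the week-12 primary contrast names PANSS total, contradicting the declared primary outcome and the primary model, which are on PANSS positive

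*Protocol article*

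**What the plan says.** All places are in the protocol article.

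- **Abstract, Method:** "The primary endpoint will be the difference in PANSS positive scores at the end of week 12".
- **Study objectives:** the effect is to be judged "on scores on the positive subscale of PANSS in patients with clozapine-resistant schizophrenia".
- **Hypothesis:** the CBD group "will demonstrate a reduction in PANSS positive scores at the end of week 12 compared with participants receiving placebo".
- **Efficacy measures:** "The PANSS positive score will be the primary outcome". The list of secondary measures in the same section starts with "PANSS total and other subscale scores (negative scale and general psychopathology scale").
- **Outcomes, Secondary:** CBD is "compared with placebo on PANSS total scores and other PANSS subscales".
- **Data analysis, model:** "The effect of CBD relative to placebo on the outcome of 12-week positive PANSS score will be analysed using mixed model repeated measures".
- **Data analysis, contrast:** "Suitable contrasts will be used to evaluate the difference in mean total PANSS scores at the primary endpoint (week 12").

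Sample size and the text of Interim analysis also refer to PANSS positive. So does the delta adjustment in Data analysis, which shifts imputed values in steps of one PANSS positive point.

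**The concern.** In a mixed model with a treatment-by-time interaction, the week-12 contrast between arms is the primary test. The sentence that specifies this contrast names a different variable from the one the model is fitted to, and that variable is a declared secondary outcome.

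Two things are at stake. First, an analyst or reader who takes the sentence at its word would test a score for which the trial was not sized. Second, a published protocol is what the final report is compared with. As it stands, someone who later reported PANSS total as the primary result could point to a sentence in support.

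**Working it through.** **1. Which variable each part of the plan uses**

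| Section | Variable | Role |
|---|---|---|
| Abstract, Method | PANSS positive | primary endpoint |
| Study objectives | PANSS positive | primary objective |
| Hypothesis | PANSS positive | hypothesis tested |
| Outcomes, Primary | PANSS positive | primary outcome |
| Efficacy measures | PANSS positive | primary outcome |
| Sample size | PANSS positive | basis of power |
| Data analysis, model sentence | PANSS positive | primary model |
| Data analysis, delta adjustment | PANSS positive | sensitivity analysis |
| Interim analysis, text | PANSS positive | basis of interim looks |
| Outcomes, Secondary; Efficacy measures | PANSS total | secondary |
| **Data analysis, contrast sentence** | **PANSS total** | **contrast at the primary endpoint** |

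Only the last row is out of line.

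**2. Can the contrast sentence be read as a secondary analysis?** No. It refers to the primary endpoint and sits inside the description of the primary model. Secondary and exploratory outcomes get their own sentence later in the section. The other use of the total score in Data analysis, the responder proportion behind the number needed to treat, is also in a separate sentence.

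**3. Which variable do the sample-size inputs belong to?** Sample size gives a 12-week difference of 1.8 points in PANSS positive and an SD of 3.739.

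- d = 1.8 / 3.739 = 0.481, which matches the stated 0.48.
- 70 / (1 − 0.20) = 87.5, rounded up to 88, which matches the stated total.

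No difference or SD is given for PANSS total, so the power of a PANSS total test cannot be worked out from the article. How the inputs lead to 70 is a different question and does not bear on this point.

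**4. Separate check: the scale of Table 2.** I assume equal arms and a z-test. The difference at an efficacy bound is then δ = z(1 − P) × SD × √(4/n), so SD = δ / [z(1 − P) × √(4/n)].

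| n | P bound | z | √(4/n) | δ in Table 2 | Implied SD | δ if SD = 3.739 |
|---|---|---|---|---|---|---|
| 22 | 0.0089 | 2.370 | 0.426 | 15.64 | 15.48 | 3.78 |
| 44 | 0.0090 | 2.366 | 0.302 | 11.06 | 15.51 | 2.67 |
| 66 | 0.0092 | 2.357 | 0.246 | 8.99 | 15.49 | 2.17 |
| 88 | 0.0094 | 2.349 | 0.213 | 7.76 | 15.49 | 1.87 |

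The implied SD is about 15.5 at every look, roughly four times 3.739 (15.5 / 3.739 = 4.1). The bounds in Table 2 are therefore not on the scale of the PANSS positive inputs under Sample size.

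**The case against.** The strongest reply is that this is one word in one sentence and the rest of the article overrules it. The model sentence in the same section names PANSS positive, and the week-12 contrast is naturally taken from that model. The delta adjustment uses PANSS positive points. A later switch to PANSS total would contradict the abstract, objective, hypothesis, outcome sections and sample size. An article also condenses a fuller protocol.

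Most of this stands. The intent is clear, a slip is the likely cause, and the room for selective choice is limited. A reader might infer that the trial plans to run its primary test on the wrong variable. The article does not support that, because it states the primary model on the right variable and misnames it once.

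Condensation does not remove the point. Nothing is left out here: the article states a variable, and that variable conflicts with its own declared primary outcome at the step that produces the primary result.

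**Conclusion.** The contradiction is real and should be corrected. It lies in the rule for the primary test, rests on the wording alone, and changes neither the design nor the planned 88 participants.

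Three stronger conclusions might be inferred, and the article supports none of them:

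- **That the standardised effect collapses.** Dividing 1.8 by 15.5 puts a PANSS positive difference over an SD inferred from Table 2. Nothing says that the effect on the total score would be 1.8 points. On Table 2's own scale, the final bound is 7.76 / 15.49 = 0.50, close to the planned 0.48.
- **That the type I error nearly doubles.** This would need the better of two independent tests to be taken as primary. PANSS positive is a component of PANSS total, so the two scores are not expected to be independent. The article gives no correlation between them and does not plan to pick the better result.
- **That Table 2 was built on PANSS total.** The mismatch in SD is arithmetic, given equal arms and a z-test, but its cause is unknown. The text of Interim analysis names PANSS positive and d = 0.48. This is a separate discrepancy and adds no weight to the wording error.

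**What to change.** In the contrast sentence under Data analysis, replace *total* with *positive*, so that the week-12 comparison is of mean PANSS positive scores. If a PANSS total contrast is wanted, state it separately and label it secondary. Make the correction before anyone sees data by arm, and carry it into any analysis plan that repeats the sentence.

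Separately, confirm which scale and SD were used for Table 2 and the interim program, and either reconcile them with the 3.739 under Sample size or explain the difference.

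The cost is one word and one check of the interim calculations. The sample size, visits and data collection stay as they are.

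### The same-approach rule for all other outcomes is too broad: it does not fit dropout or adverse-event counts, and it leaves two-visit outcomes without baseline adjustment in the lead analysis

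*Protocol article*

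**What the plan says.** The Data analysis section of the protocol article analyses the 12-week PANSS positive score by "mixed model repeated measures with fixed effects for treatment arm, time, study site, and treatment arm × time interaction". It adds: "A random intercept will be included to account for variation in scores between participants". On covariance it says: "An unstructured variance–covariance structure will be assumed, and where there are convergence issues, a compound symmetry covariance structure will be used instead". The contrast of interest is the difference in mean scores at week 12. On missing values: "Missing data will be imputed using multiple imputation by chained equations (MICE) under an assumption of missing at random". Baseline-adjusted analysis appears only as a secondary check: "A further sensitivity analysis will be conducted using an alternative analysis of covariance model plus MICE".

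The next sentence extends all of this: "All other secondary and/or exploratory outcomes will be analysed using the same approach". No exception is named.

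The outcomes listed under the heading Secondary include safety and tolerability, "as measured by the number of participants reported to have dropped out, number of adverse events reported". The Participant safety section also presents these as a secondary objective and names no statistical method. Table 1 marks dropout once, at week 12, and adverse events at all seven visits from week 0 to week 12. It marks most efficacy scales at weeks 0 and 12 only.

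**The concern.** One sentence carries a model built for a continuous score with four visits over to outcomes of quite different kinds.

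For dropout and adverse events, the rule as worded calls for a linear comparison of means at week 12 with imputation. Safety is a declared aim of the trial, so its comparison should not rest on a rule that does not suit the data.

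For outcomes measured twice, the difficulty is efficiency. The lead contrast compares week-12 means and makes no use of the baseline value already collected on the same participants. In a trial of 88, wider intervals than necessary on most secondary efficacy outcomes are a real loss.

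**Working it through.** **1. Dropout and adverse events against the rule.**
- Dropout has one value per participant. There is no time profile, no arm-by-time term and no within-participant variation for a random intercept to describe. Its value is always known, so multiple imputation has nothing to fill in.
- Adverse events are recorded at seven visits. A week-12 contrast of visit counts would use one of the seven and ignore six. A linear model of means is also a poor fit to sparse counts.
- If imputation were applied to event counts, it would assign unreported events to people who had left. At the 20% dropout allowed for under Sample size, that is 0.20 × 88 = 17.6, about 18 participants.

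**2. How many outcomes have two visits.** Efficacy rows of Table 1, leaving out height (measured once):
- Weeks 0, 4, 8 and 12: body weight, waist measures, heart rate, blood pressure, PANSS = 5.
- Weeks 0 and 12 only: lipids, HbA1c, NAFLD/FIB-4 (3); GAF, SIMPAQ, AQoL-4D, CGI, TOPF (5); four BACS rows (4); HRSA, CDSS, TMT, FCI, AUDIT, PSQI (6) = 18.
- Total 5 + 18 = 23.

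**3. Can the model be fitted to two visits?** The sample-size text counts four PANSS timepoints, which matches weeks 0, 4, 8 and 12, and no baseline covariate is listed. Baseline is therefore a response, and a two-visit outcome has two repeated measures. Covariance parameters against what the data can identify:

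| Structure | Two visits | Four visits |
|---|---|---|
| Unstructured alone | 3 parameters, rank 3 | 10, rank 10 |
| Random intercept, independent residuals | 2, rank 2 | 2, rank 2 |
| Unstructured + random intercept | 4, rank 3 | 11, rank 10 |
| Compound symmetry + random intercept | 3, rank 2 | 3, rank 2 |

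Either of the first two works with two visits. In 200 simulated trials with the random intercept alone (N = 88, correlation 0.6; four sites and 20% missing at week 12 assumed), all 200 fits converged, with a mean week-12 contrast of −1.77 against a true −1.8. Those fits did not include the unstructured matrix, so they show that a two-visit model is workable, not that the literal combination is. The combination has one parameter too many at any number of visits, including the primary PANSS model.

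**4. What the lead contrast costs.** With baseline as a response and arm means free at both visits, the complete-data week-12 contrast is essentially the raw difference. Assume equal variances at the two visits and correlation r between them. Variances relative to the raw contrast:
- ANCOVA: 1 − r²
- Change score: 2(1 − r)
- ANCOVA relative to change score: (1 − r²) / [2(1 − r)] = (1 + r)/2

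| r | ANCOVA / raw | Change / raw | ANCOVA / change |
|---|---|---|---|
| 0.4 | 1 − 0.16 = 0.84 | 1.20 | 0.70 |
| 0.6 | 1 − 0.36 = 0.64 | 0.80 | 0.80 |
| 0.8 | 1 − 0.64 = 0.36 | 0.40 | 0.90 |

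At r = 0.6, ANCOVA has 36% less variance than the raw contrast and 20% less than the change score.

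**The case against.** The best defence on safety is that the sentence was meant for efficacy scores. The list of secondary outcome measures under Efficacy measures omits dropout and adverse events. The Secondary section introduces safety as additional aims, Table 1 separates safety from efficacy, and Participant safety speaks of rates and numbers by group. The Data analysis section itself handles a binary endpoint, response on PANSS total, through proportions. A detailed safety model may also properly be left to an analysis plan that is not shown. Much of this stands: the intention was probably sensible, and the absence of a named safety model is not the complaint. What remains is that the sentence says all and names no exception, while these outcomes are labelled secondary in two places. It is mainly an error of scope in the wording.

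A reader might go further and infer that two-visit outcomes cannot be fitted at all, or that this sentence gives most secondary outcomes a non-identifiable model. The documents do not support either. Two visits are enough once one of the two overlapping covariance terms is dropped, and that overlap belongs equally to the primary model, so neither the two-visit schedule nor this sentence creates it.

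On efficiency, the defence is that ANCOVA is already planned, that choosing it as lead is a preference and not the repair of an error, and that 0.6 is a planning value for PANSS positive only. The last point is right, and the gain must be read as a range. The unadjusted contrast is valid; it is simply less precise than one available from the same data.

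**Conclusion.** The point holds in two limited parts.

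The sentence should not cover dropout and adverse-event counts. This rests on reading it as written; the separate safety section suggests that the authors did not intend it, so a scope correction is enough.

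For the 18 of 23 repeated efficacy rows measured only at weeks 0 and 12, the lead contrast leaves out the baseline adjustment. Making ANCOVA the lead analysis lowers the variance relative to the raw contrast by 16% at r = 0.4, 36% at 0.6 and 64% at 0.8. If the intended contrast is a change from baseline, the reduction at 0.6 is 20%. These figures assume complete data and equal variances at the two visits, and they ignore the small cost of estimating the slope. The documents give no correlation for any of the two-visit outcomes.

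**What to change.** Replace the sentence with three short rules.

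1. Continuous outcomes measured at three or more visits use the repeated-measures model, with either the unstructured matrix or the random intercept but not both. The same edit tidies the primary model and its compound-symmetry fallback.
2. Efficacy outcomes measured only at weeks 0 and 12 use ANCOVA as the lead analysis: week-12 value on arm, baseline value and site, with the multiple imputation already planned.
3. Dropout and adverse events are excluded from the rule and are not imputed. Report the proportion of participants who drop out, and the proportion with at least one event, each with a risk difference and confidence interval. Compare event numbers with a count or rate model such as Poisson or negative binomial.

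The cost is a few lines of analysis text. Every value needed is already in the visit schedule, and neither the sample size nor the primary endpoint changes.
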